## **11. ETHICAL CONSIDERATIONS**

The Principal Investigator will obtain ethical approval and clinical trial authorization by competent authorities according to local laws and regulations.

### **11.1 Institutional Review Board (IRB) / Research Ethics Board (REB)**

The protocol (and any amendments), the informed consent form, and any other written information to be given to subjects will be reviewed and approved by a properly constituted Institutional Review Board (IRB)/Research Ethics Board (REB), operating in accordance with the current federal regulations (e.g., Canadian Food and Drug Regulations (C.05.001); US Code of Federal Regulations (21CFR part 56)), ICH GCP and local regulatory requirements. A letter to the investigator documenting the date of the approval of the protocol and informed consent form will be obtained from the IRB/REB prior to initiating the study. Any institution opening this study will obtain REB IRB/REB approval prior to local initiation.

### **11.2 Informed Consent**

The written informed consent form (Appendix) will be provided to potential study subjects, and should be approved by the IRB/REB. The investigator is responsible for obtaining written informed consent from each subject, or from the subject's legally acceptable representative in the situation that the subject is unable to provide informed

consent. This should be completed prior to beginning and study procedures and treatment. The investigator should inform the subject (or legally acceptable representative) of all aspects of the study, including risks and benefits involved. Ample time should be allowed for questions prior to deciding about participating, and participation is entirely voluntary, and subjects are free to refuse entry into the study, or withdraw at any time for any reason.

The informed consent must be signed and dated by the subject, or legally acceptable representative, and by the person who conducted the informed consent discussion. A copy of this signed and dated form should be given to the subject or the legally acceptable representative. The process of obtaining informed consent should also be documented in the patient source documents.

### 11.3 Confidentiality of Subject Records

The names and personal information of study participants will be held in strict confidence. All study records (CRFS, safety reports, correspondence, etc.) will only identify the subject by initials and the assigned study identification number. The investigator will maintain a confidential subject identification list (Master List) during the course of the study. Access to confidential information (i.e., source documents and patient records) is only permitted for direct subject management and for those involved in monitoring the conduct of the study (i.e., Sponsors, CRO's, representatives of the IRB/REB, and regulatory agencies). The subject's name will not be used in any public

report of the study.

## **12.0 AUTHORSHIP**

Upon completion of this project, the results will be published in a peer-reviewed journal and presented at one or more conferences. Authorship on such publications will be decided by the study steering committee, and will be commensurate with the relative accrual of each center and the amount of individual contribution, including study design, patient accrual, and data analysis.

## **13.0 FINANCIAL SUPPORT**

This study is partially funded by a grant from the Ontario Institute of Cancer Research through funding provided by the Government of Ontario, the London Health Sciences Centre, and a philanthropic donation. The granting agencies are not directly involved in data collection or analysis.

## APPENDIX 1: ELIGIBILITY CHECKLIST

Eligibility – all answers must be YES, unless specified

|                                                                                                                                                                                            |                 |
|--------------------------------------------------------------------------------------------------------------------------------------------------------------------------------------------|-----------------|
| Has AJCC 7 th edition stage IV NSCLC or stage III not eligible for curative intent treatment                                                                                    | Yes / No |
| Intended to receive palliative RT to thorax, to a dose of 30 Gy in 10 or 20 Gy with > 5cm of esophagus in intended treatment field?                                                        | Yes / No |
| Willingness and ability to provide informed consent?                                                                                                                                       | Yes / No |
| Age $\geq$ 18                                                                                                                                                                              | Yes / No |
| Performance status: ECOG 0-3                                                                                                                                                               | Yes / No |
| Prior planned systematic treatment (chemotherapy, immunotherapy, targeted agents) is permissible, provided NOT given 2 weeks prior, concurrent with, or within 2 weeks following RT |                 |
| Concurrent palliative RT to other metastatic sites permissible (except lung and/or liver)                                                                                                  |                 |
| Life expectancy > 3 months                                                                                                                                                                 | Yes / No |

Ineligibility – all answers must be NO, unless specified

|                                                                                 |               |
|---------------------------------------------------------------------------------|---------------|
| Prior thoracic RT?                                                              | Yes/No |
| Serious medical comorbidities, which preclude the delivery of RT?               | Yes/No |
| Is patient pregnant or lactating?                                               | Yes/No |
| Inability to attend the full course of RT or planned follow-up/survey response? | Yes/No |

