### **2.1 Endpoints**

#### **Primary Endpoint:**

1. Esophageal quality of life
  - Measured by the Esophageal Cancer Subscale (ECS) of the FACT-E

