### **4.0 PATIENT SELECTION**

#### **4.1 Inclusion Criteria**

1. AJCC 7th edition stage IV NSCLC or stage III not eligible for curative intent treatment
2. Intended to receive palliative radiotherapy to the thorax, to a dose of 30 Gy

in 10 fractions or 20 Gy in 5 fractions. In either treatment arm, at least **5 cm of the esophagus** should be in the intended treatment field.

3. Willingness and ability to provide informed consent
4. ECOG performance status 0-3
5. Age 18 years or older
6. Prior or planned systemic treatment (chemotherapy, immunotherapy, targeted agents) is permissible at the discretion of the treating medical oncologist, provided that no systemic treatment is given within 2 weeks prior to RT, concurrent with RT, or within a 2-week period post RT.
7. Concurrent palliative RT to other metastatic sites is permissible other than the stomach and/or liver
8. Life expectancy > 3 months

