#### 4.2 Exclusion Criteria

1. Prior thoracic RT
2. Serious medical comorbidities, which in the opinion of the radiation oncologist preclude the delivery of RT
3. Pregnant or lactating women
4. Inability to attend the full course of RT or planned follow up/survey responses.
5. Congenital abnormalities of the esophagus or severe disorders of the esophagus (e.g. achalasia)

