### 6.5 Registration procedure and Data Collection:

#### Registration/Randomization Procedure

1. Call the coordinating centre at the Cancer Clinical Research Unit [contact] [name]) of London Health Sciences Centre (LHSC) to notify of new randomization and ask for the next patient ID number.
2. Complete the Enrollment form in REDCap prior to randomization. Signed letter of information to be completed and uploaded on to the REDCap database.

3. Notify the coordinating centre that you have completed the enrollment form and uploaded the required documents.
4. If the patient is eligible the coordinating centre will confirm via email and provide the randomization arm.

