| E1                                | I have difficulty swallowing solid foods.....          | 0                     | 1                       | 2                     | 3                      | 4                    |
| E2                                | I have difficulty swallowing soft or mashed foods..... | 0                     | 1                       | 2                     | 3                      | 4                    |
| E3                                | I have difficulty swallowing liquids .....             | 0                     | 1                       | 2                     | 3                      | 4                    |
| E4                                | I have pain in my chest when I swallow .....           | 0                     | 1                       | 2                     | 3                      | 4                    |
| E5                                | I choke when I swallow .....                           | 0                     | 1                       | 2                     | 3                      | 4                    |
| E6                                | I am able to enjoy meals with family or friends.....   | 0                     | 1                       | 2                     | 3                      | 4                    |
| C6                                | I have a good appetite .....                           | 0                     | 1                       | 2                     | 3                      | 4                    |
| E7                                | I wake at night because of coughing.....               | 0                     | 1                       | 2                     | 3                      | 4                    |
| ACT
11                         | I have pain in my stomach area.....                    | 0                     | 1                       | 2                     | 3                      | 4                    |
| C2                                | I am losing weight.....                                | 0                     | 1                       | 2                     | 3                      | 4                    |

Please circle or mark one number per line to indicate your response as it applies to the past 7 days.

| ADDITIONAL CONCERNS |                                               | Not at
all | A little
bit | Some-
what | Quite
a bit | Very
much |

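### The eligibility checklist in Appendix 1 does not match section 4: it names a different concurrent-RT site and has no row for the esophageal-disorder exclusion

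*Protocol*

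**What the plan says.** Section 4.1 item 7 states: "Concurrent palliative RT to other metastatic sites is permissible other than the stomach and/or liver". The Appendix 1 row for the same criterion states: "Concurrent palliative RT to other metastatic sites permissible (except lung and/or liver". That row has no Yes/No box.

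Section 4.2 lists five exclusions. The fifth is "Congenital abnormalities of the esophagus or severe disorders of the esophagus (e.g. achalasia". The second part of Appendix 1 is headed "Ineligibility – all answers must be NO, unless specified" and has four rows, ending with "Inability to attend the full course of RT or planned follow-up/survey response". None of them concerns esophageal disorders, and neither does any row in the eligibility part.

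Section 6.5 describes registration. The site completes an enrollment form in REDCap, uploads documents and notifies the coordinating centre. Then: "If the patient is eligible the coordinating centre will confirm via email and provide the randomization arm". Appendix 1 is not named in these steps.

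The primary endpoint is esophageal quality of life (section 2.1): "Measured by the Esophageal Cancer Subscale (ECS) of the FACT-E".

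**The concern.** A checklist that requires all answers to be YES or all to be NO states an eligibility rule of its own. Where it departs from section 4, the protocol holds two rules, and one patient can be eligible under one and ineligible under the other.

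Both departures touch the primary outcome. The FACT-E items in Appendix 4 ask about swallowing (for example "I have difficulty swallowing solid foods"), pain on swallowing, choking, stomach-area pain, appetite, weight loss and eating. A severe esophageal disorder, or RT to the stomach, could change these answers whatever the study RT does to the esophagus. As section 10.5 states the primary analysis, the scores compared are those at 2 weeks, and patients are analyzed as randomized. A patient enrolled in error would therefore stay in the comparison.

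**Working it through.** **Step 1: compare the criteria.**

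| Criterion | Section 4 | Appendix 1 | Match? |
|---|---|---|---|
| Sites barred for concurrent RT | stomach, liver (4.1 item 7) | lung, liver; no response box | No; only the liver is common |
| Prior thoracic RT | 4.2 item 1 | row present | Yes |
| Serious comorbidity precluding RT | 4.2 item 2 | row present | Yes |
| Pregnant or lactating | 4.2 item 3 | row present | Yes |
| Unable to complete RT, follow-up or surveys | 4.2 item 4 | row present | Yes |
| Esophageal abnormality or severe disorder | 4.2 item 5 | no row | No |
| Esophagus in the field | at least 5 cm (4.1 item 2; repeated in 6.1) | more than 5 cm | Differs only at exactly 5 cm |

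The ineligibility rows run unbroken and Appendix 2 follows directly, so the missing row does not look like a redaction or a loss in reading the file.

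**Step 2: follow a patient through each rule.**

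- Concurrent stomach RT: excluded by 4.1 item 7; not barred by the checklist wording.
- Concurrent RT to a lung site: barred by the checklist wording; not named in 4.1 item 7.
- Achalasia: excluded by 4.2 item 5; no checklist answer would reveal it.
- Exactly 5 cm of esophagus in the field: eligible under section 4; not under the checklist. Here the checklist is the stricter text and cannot admit a wrong patient.

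**Step 3: does this affect the sample size?** Inputs from section 10.4: effect size 0.65, two-sided alpha 0.05, power 80%, non-response 15%.

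- Evaluable per arm: 2 × (1.960 + 0.842)² / 0.65² = 37.2, rounded up to 38.
- Enrolled per arm: 38 / 0.85 = 44.7, rounded up to 45, so 90 in total.

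This is the plan's figure. The exact t-test version gives 39 evaluable and 39 / 0.85 = 45.9, so 46 per arm and 92 in total, which is close enough. Nothing in the calculation depends on the checklist, and correcting the checklist leaves N at 90.

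**Step 4: illustration of dilution. The shares are assumptions; the protocol gives none.** Suppose a share f of each arm has ECS scores driven by other causes and gains nothing from sparing. The effect size becomes 0.65 × (1 − f). If these patients' scores also sit s standard deviations away from the rest, the SD grows by √(1 + f(1 − f)s²). Power of the t-test with 45 × 0.85 = 38.25 evaluable per arm:

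| Assumed share f | SD unchanged | s = 1 | s = 2 |
|---|---|---|---|
| 0% | 80.1% | – | – |
| 2% | 78.5% | 77.7% | 75.4% |
| 5% | 76.0% | 74.0% | 68.6% |
| 10% | 71.4% | 67.7% | 58.1% |

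Worked case: f = 5%, s = 1 gives 0.65 × 0.95 / √1.0475 = 0.603, hence 74.0%. The table shows the direction of the effect and how it grows with f. It does not estimate what would happen in this trial.

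**The case against.** The strongest reply is that Appendix 1 may not decide anything. Section 4 still carries both criteria. Section 6.5 relies on a REDCap form and on confirmation by the coordinating centre; that form is not shown and may list every exclusion correctly. History and physical examination are mandatory (section 5.0). The esophagus is contoured over its full length and the radiation oncologist signs the fields before randomization (section 6.04 and the OAR text that follows it). The concurrent-RT row has no box, so it can be read as a note and not as a question.

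Much of this stands. A reader might infer that the checklist is the form sites complete before randomization. The protocol does not say so; its title and its all-YES/all-NO instruction suggest screening use, and no more. A reader might also infer that the primary comparison is biased. Randomization does not support that: such patients are expected in both arms alike, so the expected result is noise or dilution with no set direction. Finally, one could assume a large score shift in a single patient and express it as a fraction of the 2 to 3 points that section 10.4 calls clinically relevant. The protocol gives neither such a shift nor a frequency, so the result would only restate the assumption.

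The reply does not remove the mismatch. The other safeguards work only if someone goes back to section 4, and the missing box means that Appendix 1 records no answer on concurrent RT.

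**Conclusion.** The point holds as an internal inconsistency in the eligibility criteria. Appendix 1 and section 4 give different site lists for concurrent RT, and Appendix 1 omits one of the five exclusions. The consequence is conditional: someone screened with Appendix 1 alone could be cleared against section 4. The effect on the ECS contrast would be added noise or dilution, of unknown size. It is likely to be small if such patients are rare, but the protocol gives no frequency from which to judge this. The sample size of 90 is not in question. The 5 cm wording is housekeeping only. The correction is worth making because both mismatches concern symptoms that the primary endpoint measures, and because it costs little.

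**What to change.** - Reconcile the concurrent-RT site list between section 4.1 item 7 and Appendix 1. The sponsor's clinical leads decide which list stands; this review takes no position.
- Give that checklist row a Yes/No box so that the answer is recorded.
- Add the section 4.2 item 5 exclusion to Appendix 1 as a fifth ineligibility row.
- Confirm that the REDCap enrollment form carries the same reconciled criteria, and correct it only if it does not.
- Use one wording for the 5 cm esophagus criterion throughout.

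The cost is an edit to the checklist, plus an edit to section 4.1 if the leads choose the other list, and a check of the enrollment form. The sample size and the analysis do not change.

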## Appendix 2 – Follow-up schedule

|                       | pre-RT                       | 2 weeks post RT | *4, 8 weeks post RT            | Months 3, 6, 12        |
|-----------------------|------------------------------|-----------------|--------------------------------|------------------------|
| History and physical, | X                            | X               | Only if clinic visit is booked | X                      |
| *Toxicity scoring     | X                            | X               | X                              | X                      |
| CT chest              | X                            |                 |                                | Suggested and optional |
| Bone scan             | Recommended if bony symptoms |                 |                                |                        |
| CT or MRI brain       | Recommended if CNS symptoms  |                 |                                |                        |
| *FACT-E and FACT-L    | X                            | X               | X                              | X                      |
| *EQ-5D                | X                            | X               | X                              | X                      |

\* QoL forms and toxicity scoring may also be completed via telephone for all follow up visits (but not preferred) if patient prefers or is unable to attend clinic. For non-English patients, a fluent family member, staff, or professional translator may assist with completion of the questionnaire. The FACT-E and FACT-L are also available in the following languages (contact the coordinating centre or [www.facit.org](http://www.facit.org) for these):

Chinese (simplified or traditional), Dutch, French, German, Hungarian, Italian, Japanese, Polish, Spanish

### Appendix 3 – Letter of Information (to follow)

#### Appendix 4 – FACT-G, FACT-E, FACT-L, EQ-5D Quality of Life Forms

Below is a list of statements that other people with your illness have said are important.

**Please circle or mark one number per line to indicate your response as it applies to the past 7 days.** This questionnaire will only take 5-10 minutes to complete.

|                                   |                                                                                      | Not
at all | A little
bit | Some
-what | Quite
a bit | Very
much |
|-----------------------------------|--------------------------------------------------------------------------------------|---------------|-----------------|---------------|----------------|--------------|
| PHYSICAL WELL-BEING |                                                                                      |               |                 |               |                |              |
| GP1                               | I have a lack of energy .....                                                        | 0             | 1               | 2             | 3              | 4            |
| GP2                               | I have nausea .....                                                                  | 0             | 1               | 2             | 3              | 4            |
| GP3                               | Because of my physical condition, I have trouble meeting the needs of my family..... | 0             | 1               | 2             | 3              | 4            |
| GP4                               | I have pain.....                                                                     | 0             | 1               | 2             | 3              | 4            |
| GP5                               | I am bothered by side effects of treatment.....                                      | 0             | 1               | 2             | 3              | 4            |
| GP6                               | I feel ill .....                                                                     | 0             | 1               | 2             | 3              | 4            |
| GP7                               | I am forced to spend time in bed.....                                                | 0             | 1               | 2             | 3              | 4            |

|                                        |                                                                                                                                                                                                             | Not
at all | A little
bit | Some
-what | Quite
a bit | Very
much |
|----------------------------------------|-------------------------------------------------------------------------------------------------------------------------------------------------------------------------------------------------------------|---------------|-----------------|---------------|----------------|--------------|
| SOCIAL/FAMILY WELL-BEING |                                                                                                                                                                                                             |               |                 |               |                |              |
| GS1                                    | I feel close to my friends .....                                                                                                                                                                            | 0             | 1               | 2             | 3              | 4            |
| GS2                                    | I get emotional support from my family .....                                                                                                                                                                | 0             | 1               | 2             | 3              | 4            |
| GS3                                    | I get support from my friends .....                                                                                                                                                                         | 0             | 1               | 2             | 3              | 4            |
| GS4                                    | My family has accepted my illness .....                                                                                                                                                                     | 0             | 1               | 2             | 3              | 4            |
| GS5                                    | I am satisfied with family communication about my illness.....                                                                                                                                              | 0             | 1               | 2             | 3              | 4            |
| GS6                                    | I feel close to my partner (or the person who is my main support).....                                                                                                                                      | 0             | 1               | 2             | 3              | 4            |
| Q1                                     | Regardless of your current level of sexual activity, please answer the following question. If you prefer not to answer it, please mark this box  and go to the next section. |               |                 |               |                |              |
| GS7                                    | I am satisfied with my sex life .....                                                                                                                                                                       | 0             | 1               | 2             | 3              | 4            |

Please circle or mark one number per line to indicate your response as it applies to the past 7 days.

| EMOTIONAL WELL-BEING |                                                           | Not
at all | A little
bit | Some
-what | Quite
a bit | Very
much |
|------------------------------------|-----------------------------------------------------------|-----------------------|-------------------------|-----------------------|------------------------|----------------------|
| GE1                                | I feel sad.....                                           | 0                     | 1                       | 2                     | 3                      | 4                    |
| GE2                                | I am satisfied with how I am coping with my illness ..... | 0                     | 1                       | 2                     | 3                      | 4                    |
| GE3                                | I am losing hope in the fight against my illness .....    | 0                     | 1                       | 2                     | 3                      | 4                    |
| GE4                                | I feel nervous .....                                      | 0                     | 1                       | 2                     | 3                      | 4                    |
| GE5                                | I worry about dying .....                                 | 0                     | 1                       | 2                     | 3                      | 4                    |
| GE6                                | I worry that my condition will get worse .....            | 0                     | 1                       | 2                     | 3                      | 4                    |

| FUNCTIONAL WELL-BEING |                                                         | Not
at all | A little
bit | Some
-what | Quite
a bit | Very
much |
|-------------------------------------|---------------------------------------------------------|-----------------------|-------------------------|-----------------------|------------------------|----------------------|
| GF1                                 | I am able to work (include work at home).....           | 0                     | 1                       | 2                     | 3                      | 4                    |
| GF2                                 | My work (include work at home) is fulfilling .....      | 0                     | 1                       | 2                     | 3                      | 4                    |
| GF3                                 | I am able to enjoy life .....                           | 0                     | 1                       | 2                     | 3                      | 4                    |
| GF4                                 | I have accepted my illness .....                        | 0                     | 1                       | 2                     | 3                      | 4                    |
| GF5                                 | I am sleeping well .....                                | 0                     | 1                       | 2                     | 3                      | 4                    |
| GF6                                 | I am enjoying the things I usually do for fun.....      | 0                     | 1                       | 2                     | 3                      | 4                    |
| GF7                                 | I am content with the quality of my life right now..... | 0                     | 1                       | 2                     | 3                      | 4                    |

Please circle or mark one number per line to indicate your response as it applies to the past 7 days.

| ADDITIONAL CONCERNS |                                                        | Not
at all | A little
bit | Some
-what | Quite
a bit | Very
much |
|-----------------------------------|--------------------------------------------------------|-----------------------|-------------------------|-----------------------|------------------------|----------------------|
| HN1                               | I am able to eat the foods that I like.....            | 0                     | 1                       | 2                     | 3                      | 4                    |
| HN2                               | My mouth is dry.....                                   | 0                     | 1                       | 2                     | 3                      | 4                    |
| HN3                               | I have trouble breathing.....                          | 0                     | 1                       | 2                     | 3                      | 4                    |
| HN4                               | My voice has its usual quality and strength.....       | 0                     | 1                       | 2                     | 3                      | 4                    |
| HN5                               | I am able to eat as much food as I want.....           | 0                     | 1                       | 2                     | 3                      | 4                    |
| HN
10                          | I am able to communicate with others .....             | 0                     | 1                       | 2                     | 3                      | 4                    |
| HN7                               | I can swallow naturally and easily .....               | 0                     | 1                       | 2                     | 3                      | 4                    |
| E1                                | I have difficulty swallowing solid foods.....          | 0                     | 1                       | 2                     | 3                      | 4                    |
| E2                                | I have difficulty swallowing soft or mashed foods..... | 0                     | 1                       | 2                     | 3                      | 4                    |
| E3                                | I have difficulty swallowing liquids .....             | 0                     | 1                       | 2                     | 3                      | 4                    |
| E4                                | I have pain in my chest when I swallow .....           | 0                     | 1                       | 2                     | 3                      | 4                    |
| E5                                | I choke when I swallow .....                           | 0                     | 1                       | 2                     | 3                      | 4                    |
| E6                                | I am able to enjoy meals with family or friends.....   | 0                     | 1                       | 2                     | 3                      | 4                    |
| C6                                | I have a good appetite .....                           | 0                     | 1                       | 2                     | 3                      | 4                    |
| E7                                | I wake at night because of coughing.....               | 0                     | 1                       | 2                     | 3                      | 4                    |
| ACT
11                         | I have pain in my stomach area.....                    | 0                     | 1                       | 2                     | 3                      | 4                    |
| C2                                | I am losing weight.....                                | 0                     | 1                       | 2                     | 3                      | 4                    |

Please circle or mark one number per line to indicate your response as it applies to the past 7 days.

| ADDITIONAL CONCERNS |                                               | Not at
all | A little
bit | Some-
what | Quite
a bit | Very
much |
|----------------------------|-----------------------------------------------|---------------|-----------------|---------------|----------------|--------------|
| B1                         | I have been short of breath .....             | 0             | 1               | 2             | 3              | 4            |
| C2                         | I am losing weight.....                       | 0             | 1               | 2             | 3              | 4            |
| L1                         | My thinking is clear .....                    | 0             | 1               | 2             | 3              | 4            |
| L2                         | I have been coughing .....                    | 0             | 1               | 2             | 3              | 4            |
| B5                         | I am bothered by hair loss .....              | 0             | 1               | 2             | 3              | 4            |
| C6                         | I have a good appetite .....                  | 0             | 1               | 2             | 3              | 4            |
| L3                         | I feel tightness in my chest.....             | 0             | 1               | 2             | 3              | 4            |
| L4                         | Breathing is easy for me.....                 | 0             | 1               | 2             | 3              | 4            |
| Q3                         | Have you ever smoked?
No____Yes____If yes: |               |                 |               |                |              |
| L5                         | I regret my smoking .....                     | 0             | 1               | 2             | 3              | 4            |

Under each heading, please tick the ONE box that best describes your health TODAY.

